#### Outcome 5: Sustainability.

For this outcome, we will evaluate the impact of CDSS on environmental sustainability. Energy consumption and carbon emissions were approximated from established radiology literature (X-ray Cervical and Lumbar Spine – 0.91 kWh, 1.6 kg CO_2_e) [43–45].

Similar to the thread on radiation dose, we will compare the pre-implementation data on the volume of spine imaging referrals with post-implementation data of the same duration, focusing on the changes in the volume of the overall imaging utilisation before and after the interventions. We will estimate the carbon emissions and energy consumption reduction based on before vs. after implementation data. Similarly, we will also calculate the carbon emissions and energy consumption from imaging tests prevented, using the formula “carbon emissions/energy consumption X number of imaging avoided”.

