#### Outcome 4: Radiation dose.

The established literature “Radiology: Patient Exposure from Radiologic and Nuclear Medicine Procedures in the United States: Procedure Volume and Effective Dose for the Period 2006–2016” will serve as the basis for estimating the radiation dose to patients [42]. The publication, based on the International Commission on Radiological Protection (ICRP) Publication 60, indicates an effective dose per scan of 0.36 mSv for X-rays of the Cervical Spine and 1.4 mSv for the Lumbar Spine. We will establish the cumulative effective dose associated with the imaging tests and highlight the comparison of the relative contributions of appropriate and inappropriate imaging with the total number of examinations and the total collective effective dose. We will also evaluate the number of imaging tests avoided (i.e., physician after consulting CDSS followed CDSS recommendations on not referring patient(s) for imaging) and the associated radiation dose prevented using the formula: “effective dose per scan X number of imaging avoided”.

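### Energy and carbon savings rest on crude before-after X-ray volume, with no patient denominator or control subtraction, and the separate count of avoided imaging has no counterfactual

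*Protocol article*

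**What the plan says.** Outcome 5 states a causal aim: "we will evaluate the impact of CDSS on environmental sustainability". Its method is to set pre-implementation volume against "post-implementation data of the same duration", "focusing on the changes in the volume of the overall imaging utilisation before and after the interventions". The conversion follows: "We will estimate the carbon emissions and energy consumption reduction based on before vs. after implementation data", with unit values of "0.91 kWh, 1.6 kg CO_2_e" per X-ray.

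A second measure runs beside it. Outcome 4 defines imaging avoided as cases in which the "physician after consulting CDSS followed CDSS recommendations on not referring patient(s) for imaging", and computes dose prevented as "effective dose per scan X number of imaging avoided", with unit doses of "0.36 mSv for X-rays of the Cervical Spine and 1.4 mSv for the Lumbar Spine". Outcome 5 multiplies the same count by the carbon and energy units.

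Three other sections bear on this. Comparator and intervention describes a dataset of consecutive patients who were referred for spine radiography. It also forms the two groups by the date on which a physician's posting starts. Data and statistical analysis plans before-after t-tests for both groups; its only phase-by-arm interaction sits in the patient-level logistic model, which is for appropriateness.

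**The concern.** Two periods of equal length are not two periods with equal numbers of patients. The X-ray count of a fixed set of physicians depends on how many patients they see, and so on attendance, rota and leave, as well as on how readily they order. Only the ordering behaviour is something the CDSS can change. Without a denominator, or at least the control group's change taken off, the two cannot be separated, and the whole difference would be presented as impact of the CDSS.

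The avoided count has a different fault. It can arise only in the intervention group's second phase, so neither the first phase nor the control group offers anything to compare it with. It cannot fall below zero. It may include patients whom the physician would not have sent for X-ray anyway. A positive total could therefore be reported as dose, energy and carbon prevented even if imaging per patient had not changed.

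**Working it through.** **The plan's own figures.** The article states no expected energy, carbon or dose saving, so there is none to reproduce. The only count available as a scale is the 235 per group in Sample size. It reproduces from the stated inputs (effect size 0.3, two-sided alpha 0.05, power 0.9): the normal approximation gives 234 per group, 468 in total, and the exact two-sample t calculation gives 234.46, rounded up to 235. It is a sample size for the primary comparison, not a forecast of X-ray volume. It is used below only to give the effect a size.

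**Inputs.** 0.91 kWh and 1.6 kg CO2e per X-ray (Outcome 5). Assumed: 235 X-rays in the first phase, and the workload changes shown. The documents give no workload figures.

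**Formula as written.** Saving = (X-rays before − X-rays after) × unit value.

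**Case 1: no CDSS effect, workload falls.**

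| Fall in patients seen | Fewer X-rays | kWh | kg CO2e |
|---|---|---|---|
| 5% | 0.05 × 235 = 11.75 | 11.75 × 0.91 = 10.7 | 11.75 × 1.6 = 18.8 |
| 10% | 0.10 × 235 = 23.5 | 23.5 × 0.91 = 21.4 | 23.5 × 1.6 = 37.6 |
| 20% | 0.20 × 235 = 47 | 47 × 0.91 = 42.8 | 47 × 1.6 = 75.2 |

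Per patient seen, or net of a control group with the same workload change, the saving in every row is zero.

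**Case 2: a true 10% cut in X-rays per patient.** The adjusted saving compares the second phase with what the same workload would have produced without the cut.

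- Workload down 10%: after = 235 × 0.9 × 0.9 = 190.35. Crude saving = 235 − 190.35 = 44.65 X-rays, or 71.4 kg. Adjusted = 211.5 − 190.35 = 21.15 X-rays, or 33.8 kg.
- Workload up 10%: after = 235 × 1.1 × 0.9 = 232.65. Crude saving = 235 − 232.65 = 2.35 X-rays, or 3.8 kg. Adjusted = 258.5 − 232.65 = 25.85 X-rays, or 41.4 kg.

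The same true effect appears about twice too large in one direction and nearly vanishes in the other.

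**Chance variation.** If the counts were Poisson (an assumption), the before-after difference would have a 95% range of ±1.96 × √(2 × 235) = ±42 X-rays, about 18% of 235. This is random error, not workload bias, and a denominator would not remove it. It is the reason why any converted saving needs a confidence interval.

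**Can the planned analyses repair this?** The dataset described holds imaged patients only, so a rate per patient seen cannot be formed from it. The logistic model has the needed interaction, but its outcome is whether an X-ray was appropriate, given that it was ordered; it cannot model how many were ordered.

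**The case against.** The strongest reply is that the control data are not ignored. The t-test is planned for both groups, Strengths presents the control group as the means of showing change over time, and Limitations promises to account for changes that could affect outcomes and urges caution about the attributable effect. These are also exploratory outcomes built on literature unit values, and the model for a secondary count could be left to an analysis plan. What stands is that the control change could be displayed. But none of these statements gives a method for volume, and Limitations itself says that the two groups are not directly compared. The estimator is stated, not left open, and it is the stated estimator that fails.

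A second reply is that physicians must leave the ordering system to open the CDSS, so a consultation suggests that an X-ray was intended. That makes it less likely that the avoided count includes patients who would not have been imaged; it does not exclude it.

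Some stronger readings are tempting but not supported:

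- A reader might infer that a fall in workload would also be booked as dose prevented. Outcome 5 does liken its comparison to the one for dose, but Outcome 4 gives no before-after volume formula; dose prevented uses the avoided count alone. Fewer patients would, if anything, make that count smaller.
- A reader might take the avoided count to be every consultation that ended without an order. It is narrower: the CDSS must have advised against imaging and the physician must have followed.
- A reader might extend the fault to Outcome 3. The cost formula multiplies the number of inappropriate X-rays by unit cost and uses neither volume change nor the avoided count.

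**Conclusion.** The point holds for energy and carbon in Outcome 5: the plan claims an impact of the CDSS but computes a quantity that mixes ordering behaviour with workload. On the assumed scale of 235 X-rays in the first phase, each 10% change in patients seen moves the result by 23.5 X-rays, 21.4 kWh and 37.6 kg CO2e with no CDSS effect at all. The error can create a saving or hide one. The workload changes are assumed, so these figures show sensitivity and are not a forecast.

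The avoided count is a separate fault of interpretation. It describes use of the CDSS and should not be reported as dose, energy or carbon prevented by it.

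These are secondary outcomes. The primary appropriateness rate has its own denominator and is not touched.

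**What to change.** 1. Report spine X-rays per 100 encounters seen by the recruited physicians, by phase and arm. All encounters in acuity categories P3 and P4 would serve as the denominator: an aggregate count per physician and phase, which avoids having to identify every spine patient who was not imaged.
2. Estimate the CDSS effect as the phase-by-arm contrast in a Poisson or negative-binomial model, with the log of encounters as offset and physician effects.
3. Convert that net number, with its confidence interval, to kWh and CO2e, and to mSv with the separate cervical and lumbar unit doses.
4. Keep the avoided count, labelled as a description of CDSS use, and drop the claim that it measures what was prevented.

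Both the denominator and the control contrast are needed. Because groups are formed by posting date, the control group's phases may fall in other calendar months, and subtracting its change may then not remove workload differences by itself.

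The cost is one more extract of encounter counts and one more model; control X-ray data are already collected in both phases. The price in results is wider, possibly null, savings estimates.

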### Data management plan

No coded/anonymous research data will be sent outside of the study’s institution. We will code the collected data to prevent participant identification. We will store the data in the encrypted/password-protected healthcare cloud (H-cloud), which is the private cloud of Singapore public healthcare. Once the study concludes, we will retain the data for a maximum of seven years before erasing the soft copy. The research data will only be accessible to the PI, who will treat all personal information and results with complete confidentiality. Only authorised personnel will review the data to ensure correct study execution. The PI will also perform data and safety monitoring. The PI will review the recruited data on a monthly basis, and since this study poses only minimal risk, data integrity monitoring is not required. Similarly, this research study does not have any stopping criteria based on efficacy, futility, or safety considerations.

### Safety considerations

There is no expected physical, psychological, social, or economic harms associated with this study. The participants will receive complete information regarding the study design and the scientific rationale underlying the proposed study.

The research team is multidisciplinary and comprises radiographers, EM physicians, and radiologists with sufficient expertise and experience to conduct the research. Data are collected from routine (cervical and lumbar spine X-rays) procedures to avoid unnecessary risk to patients. The PI, who is neither from the ED nor has any relationship with the participants, will perform the data analysis, minimising privacy and confidentiality risks. Additionally, the information will not be used for any purpose except for this research, and that participants will never be identified personally; only group data will be reported.

### Data and statistical analysis

We will describe participant and patient demographics, clinical and imaging characteristics, and study outcomes using standard methods, such as frequencies and percentages for categorical variables and mean, standard deviation, median, and range for continuous variables.

We will use a t-test to examine the outcomes before and after the intervention (“Do nothing” and CDSS). The primary outcome (appropriateness) is binary at the patient level but analysed at the physician (cluster) level. Each physician’s mean appropriateness in the pre- and post-phases will be compared using a paired t-test on within-physician differences; if assumptions of normality are materially violated, analyses will be repeated with a variance-stabilising transformation.

To complement this, patient-level multilevel logistic regression models will be performed with a random intercept for physician and fixed effects for phase, intervention arm, and their interaction. Patient-level (age, sex, indication type) and physician-level (specialty) covariates will be included to adjust for potential confounding. Both unadjusted cluster-level and adjusted multilevel estimates will be reported side by side. Where possible, we will present all effects with confidence intervals.

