#### Outcome 2: Clinical effectiveness.

Addressing clinical effectiveness is critical to answering the question, “What is the impact of CDSS on patient outcome(s)?”. To assess the clinical effectiveness of CDSS in the real world, we will examine the clinically significant positive rates of imaging procedures performed, in tandem with the subsequent patient dispositions (i.e., treated and discharge, admission, referral to specialist, referral to physiotherapy and “At Own Risk”) at the end of the individual patient journey in the ED. The radiological reports of associated imaging procedures will be evaluated for significant positive findings that will impact therapeutic decisions, such as fractures in both the cervical and lumbar spines and soft tissue swelling in the cervical spine (i.e., fracture or prevertebral soft tissue swelling – sign of cervical spine jury, were considered positive; all else considered negative). To facilitate comparison in the proportions of positive findings among the categories, we will assess the imaging positivity rates in both the appropriate and inappropriate imaging cohorts. By using a longitudinal approach to monitor patients until their disposition, we will be able to clarify the risks physicians face regarding patient safety and quality of care, particularly in relation to the question: “What impact will following or not following imaging recommendations from the guidelines have on patient outcomes?” [41].

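### Outcome 2 asks what the CDSS does to patient outcomes, but neither the contrast it names nor the general before-after t-test gives a control-adjusted effect, and the t-test does not fit five-category disposition

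*Protocol article*

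**What the plan says.** Under Outcome 2 (Clinical effectiveness) the protocol article poses two questions. The first is "What is the impact of CDSS on patient outcome(s", followed by a closing bracket and question mark. The second, at the end of the section, is "What impact will following or not following imaging recommendations from the guidelines have on patient outcomes".

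Two measures are named:
- **Positivity** of each X-ray. It is binary: defined findings "were considered positive; all else considered negative".
- **Disposition** at the end of the ED visit. It has five unordered categories: "treated and discharge, admission, referral to specialist, referral to physiotherapy and “At Own Risk".

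The one comparison the section spells out is "we will assess the imaging positivity rates in both the appropriate and inappropriate imaging cohorts".

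The section on data and statistical analysis gives descriptive summaries ("frequencies and percentages for categorical variables") and then the general sentence "We will use a t-test to examine the outcomes before and after the intervention", which applies to both groups and excepts no outcome. It goes on to specify a paired t-test on physician-level means for appropriateness. As a complement to that, it plans patient-level multilevel logistic models with a physician random intercept and "fixed effects for phase, intervention arm, and their interaction".

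**The concern.** The first question is about the CDSS, so its answer needs a comparison of phases between arms. The comparison written under Outcome 2 sorts X-rays by whether they met the guideline. It describes how well the guideline separates positive from negative films, and it can come out the same whether or not the CDSS changed practice.

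The general t-test sentence does bring in phase, but only within each group. The protocol's Introduction and Strengths sections justify the control group as the basis for attributing change to the CDSS, and two separate within-group tests do not use it for that purpose. For disposition there is a further problem: a nominal variable has no mean, so a t-test on it has no defined meaning without a coding that the plan does not give.

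Outcome 2 is secondary, but it is where the protocol addresses patient safety and quality of care. If the text is followed literally, the report could present the appropriate/inappropriate gap, or a within-group p-value, as the effect of the CDSS on patients.

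**Working it through.** **Inputs.** The documents give no positivity or disposition figures for this outcome and no sample size for it. From the Sample size section come 20% inappropriate imaging and 235 patients per phase. All other rates and counts below are assumptions, used only to show how the methods behave.

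**The plan's own figure.** With effect size 0.3, power 0.9 and two-sided alpha 0.05, n per group = 2 × (1.960 + 1.282)² / 0.3² ≈ 233.5, so 234 (468 in total). The t-distribution solution is 234.5, so 235. The stated 468 and 235 are reproduced. Nothing below depends on them except the choice of 235 for the illustration.

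**Step 1: what the named contrast measures.** Let a and b be positivity in appropriate and inappropriate X-rays, and q the share that is inappropriate. The named contrast is a − b. Overall positivity is a(1 − q) + bq. Suppose the CDSS lowers q from 20% to 8% and leaves a and b unchanged:

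| Assumed a / b | Gap a − b, q = 20% | Gap a − b, q = 8% | Overall positivity, q = 20% | Overall positivity, q = 8% |
|---|---|---|---|---|
| 10% / 2% | 8 points | 8 points | 0.10×0.80 + 0.02×0.20 = 8.4% | 0.10×0.92 + 0.02×0.08 = 9.36% |
| 10% / 5% | 5 points | 5 points | 9.0% | 9.6% |
| 6% / 3% | 3 points | 3 points | 5.4% | 5.76% |

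When positivity within each class is unchanged, the gap does not register that the CDSS worked.

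**Step 2: what the within-group t-test leaves out.** The control-adjusted effect is (after − before in the CDSS arm) − (after − before in the control arm). Take the first row for the CDSS arm, a change of 9.36 − 8.4 = 0.96 points. If the control arm stays at 8.4%, the adjusted effect is 0.96 − 0 = 0.96 points. If the control arm also moves to 9.36%, it is 0.96 − 0.96 = 0. The before-after test in the CDSS arm is identical in the two cases. The phase-by-arm interaction estimates this comparison on the log-odds scale.

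**Step 3: a t-test on a nominal variable.** Assume 235 patients per phase, dispositions 150/30/30/20/5 before and 125/55/30/20/5 after, and ignore clustering.
- Chi-square on the 2 × 5 table: 9.63 on 4 degrees of freedom, p = 0.047.
- t-test with codes 1 to 5 in the order the protocol lists the categories: means 1.72 and 1.83, p = 0.29.
- t-test over all 120 assignments of codes 1 to 5: p from 0.003 to 0.43, with 60 of the 120 below 0.05.

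The data are the same each time and only the labels change. This shows why the test does not suit the variable. It does not predict what the trial will find.

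**Step 4: where the suitable model sits.** The multilevel paragraph comes directly after the physician-level analysis of appropriateness and is introduced as a complement to it. It has the needed structure (physician clustering, phase, arm, interaction) for a binary outcome, but no sentence assigns it to positivity. No inferential method for a nominal outcome is named. By contrast, Outcome 5 states its pre/post comparison explicitly; Outcome 2 does not.

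**The case against.** - **The plan does contain a before-after comparison.** The t-test sentence covers the outcomes in both groups and can be read to include Outcome 2. Positivity is binary, so physician-level rates could be compared just as appropriateness is. This stands. A reader might infer that the planned analysis cannot address the first question at all; the text does not support that. What is missing is the between-arm estimate.
- **The appropriate/inappropriate contrast has a purpose.** It bears directly on the second question, about following recommendations. This stands: the contrast is not misplaced, but it is not an answer to the first question.
- **Nothing says disposition will be coded 1 to 5.** This also stands. Disposition may be meant only for frequencies and percentages, or to be tested one category at a time as proportions. One should not infer that the investigators will run a t-test on arbitrary codes. The range of p-values illustrates the mismatch and is not a consequence of the plan.
- **The multilevel paragraph is not restricted to appropriateness.** It speaks of models in the plural and names no outcome, so it is too strong to say the model is reserved for the primary outcome. It is simply not assigned to this one.
- **Test choice for a secondary outcome belongs in an SAP.** Silence would indeed be no finding. Here the article states a general method that does not fit one of the two measures, and a contrast that does not match its leading question. An SAP written from this text could inherit both.

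**Conclusion.** The point holds in a limited form. The contrast spelled out for Outcome 2 does not estimate a CDSS effect. The general t-test gives only within-group changes and does not fit five-category disposition. The model that would give a control-adjusted effect on positivity is already in the plan but is not tied to this outcome.

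No size can be put on the consequence from the documents. The 8-point gap that does not move rests on assumed positivity rates and on positivity within each class being unaffected by the CDSS. The p-values rest on assumed counts and ignore clustering. The primary analysis and the sample size are untouched. This should be corrected before analysis, but it does not threaten the trial's main conclusion.

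**What to change.** 1. **Positivity:** state that the planned mixed logistic model (physician random intercept; phase, arm and phase × arm) will be fitted, and report the interaction with its confidence interval as the CDSS effect.
2. **Disposition:** name a categorical analysis that allows for physician clustering, either a multinomial model or a mixed logistic model per category, with sparse categories such as At Own Risk merged by a rule set in advance. Label it exploratory.
3. **t-test sentence:** limit it to physician-level means.
4. **Appropriate versus inappropriate positivity:** keep it, labelled as answering the second question.
5. **Scope:** state that Outcome 2 results apply to imaged patients only. The Comparator and intervention section includes only patients referred for spine radiography, so patients whose X-ray was avoided are not observed, and the models above do not change that.

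The cost is a few lines of text and some extra model runs on data already planned for collection, with no change in sample size. The downsides are wide intervals for rare categories and several secondary comparisons, which is why disposition should be read as exploratory.
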